# 11 Control arm (Comparator)

The control area will continue to receive usual health services from government and other providers. All ASHAs in control and intervention area will be trained to get up-to-date to provide recommended maternal, newborn and child care. ASHAs will receive refreshers’ training based on ASHA module-6 and 7 which provides skills for the maternal care services that she is expected to deliver including counselling pregnant women, ensuring complete antenatal care through home visits and enabling care at monthly Village Health and Nutrition Days (VHND), assisting households to make birth plan and supporting households for safe delivery. Regarding newborn care, ASHAs will be trained to undertake at least 6 post-partum visits, counsel and problem solve on breastfeeding, keep the baby warm and identify and do basic management of LBW (Low Birth Weight) and pre-term baby, perform examinations needed for identification/first contract care for sepsis and asphyxiaError: Reference source not found. Size of control area will be same as intervention area (11 PHCs).

Currently, there are two e-health initiatives underway in both control and intervention areas. First one is provision of SIM card with CUG (Common User Group) at free of cost to all ASHAs. The government recharges balance of SIM on monthly basis. The ASHAs are expected to use SIM for making phone calls for patient care and other responsibilities. Mobile phones are not provided. Second initiative is Online Mother and Child Tracking System (MCTS) which is described in detail in section 2.3.

To avoid the duplication of data being entered separately into the MCTS and ImTeCHO systems, active efforts are being made to make both IT systems interoperable. There have been discussions with the state government officials to obtain necessary approval. The investigators are in contact with the developers of the MCTS, National Informatics Center (NIC), whose representatives have visited SEWA Rural to discuss this matter. The ImTeCHO system has been developed to ensure potential interoperability. We await the final decision by the state government in this regards.

The MCTS and ImTeCHO generates various reports for the PHC staff; this raises concern regarding duplication and increase in work load. However, the ImTeCHO intervention is developed so that it complements the MCTS reports. The ImTeCHO produces reports and alerts to inform the medical officer regarding a newly diagnosed high risk case; this report is not available in the MCTS. Similarly, there other reports which are not available in the MCTS and can be found only in the ImTeCHO web interface; thus, minimising duplication. Additionally, the reports from the ImTeCHO is created based on the data entered by ASHAs, whereas, the MCTS generates reports based on the data entry operator at the PHC. Therefore, there will be no additional burden at the PHC level towards entering data for generating the reports in the ImTeCHO intervention.

# 12 Measurement of outcomes and follow up

**Table 11 Measurement of outcomes**

| **What** | **Where** | **When** | **How** | **By Who** |
| --- | --- | --- | --- | --- |
| Coverage of proven maternal and newborn interventions, coverage of care among complicated maternal and newborn cases | At household level in community | 2 times: Pre-intervention (baseline), Post-intervention (end line) | Household survey as reported by mothers of infants age 1 to 3 months* | Data collection team |
| Coverage of proven young infant health interventions, coverage of care among complicated young infant cases | At household level in community | 2 times: Pre-intervention (baseline), Post-intervention (end line) | Household survey as reported by mothers of infants age 1 to 3 months | Data collection team |
| Adherence to intervention and Support and supervision received by ASHAs | From ImTeCHO program data (online) | Post-intervention (end line) | From web interface & log of ImTeCHO facilitator | Investigators |

* Mothers of infant age 6 to 8 months will be surveyed at baseline

*Data collection for all research questions*

Household surveys will be used for assessing set of indicators for primary objective, secondary objective-1 and secondary objective-4. The household survey tools is based on draft tool for district level health and facility survey (DLFHS-4) which is available online[[48]](#footnote-49). The survey tools are included in Appendix 2. Respondents will be

- For maternal, and newborn health interventions: All woman who are native of study village and is mother of an infant who is one to four months old at the time of survey will be considered as respondents for evaluation. All native women who resided most of the time (at least five months) in study cluster during antenatal period will be included. All women must be in the study cluster at the time of birth in case of home deliveries and in case of institutional deliveries if the she went to hospital from study cluster and came back to same study cluster immediately after delivery, and who provided consent for the evaluation will be included. All women who resided in study cluster for most of time during first month after delivery will be included. Women whose infant died before the survey will be excluded. Respondents will be identified through ongoing pregnancy and mortality surveillance which described later in this section.
- For child health interventions: All adult woman who are native of study village and is mother of an infant who is six to eight months old at the time of survey will be considered as respondents for evaluation. Women whose infant died before the survey will be excluded.
- For indicators reflecting supervision and support (secondary research question 2 and 3) received by ASHAs in the intervention area, program data will be used from the ImTeCHO web interface and documentation of mHealth facilitators.

All pregnancy registrations, its outcomes, any newborn and infant deaths in all clusters throughout the study period will be counted as part of ongoing pregnancy and mortality surveillance. For that, outcome of all pregnancies will be determined to ensure complete counting of all newborn deaths. This will be done by data collection team by conducting house to house survey of whole study area on regular basis. All live births to woman who are native of study village will included irrespective of place of the birth.

*Follow up*

All new pregnant women and their neonates will be enrolled through ongoing pregnancy and mortality surveillance described above. Each pregnant woman and neonate will be followed up to one year after pregnancy outcome in both arms unless the woman or neonate dies or family migrates out of study area. All clusters and ASHAs will be followed throughout the study by the team of data collectors and investigators.

# 13 Project plan and management

## 13.1 Implementation of intervention

### 13.1.1 Pre-intervention baseline household survey

- Identify validated tool such as DLHFS and modify as per need
- Train data collection team
- Pre-test data collection tool
- Create database
- Do a survey using smart-phone data collection application

### 13.1.2 Training and intervention maturation

There will be two kinds of training: refreshers’ training and secondly training of users to use ImTeCHO. SEWA Rural will provide training.

**Table 12 Type and duration of training**

| Type of training | Trainees | Duration | Timing |
| --- | --- | --- | --- |
| ASHAs’ Refreshers’ training for ASHA module 6 & 7 | All ASHAs of control and intervention area | 3 days | Training phase (5-10 months) |
| ASHAs’ training to use ImTeCHO application | All ASHAs of intervention area | 3-4 days | Training phase (5-10 months) |
| Accreditation followed by getting on production server | All ASHAs of intervention area | 3 days | Training phase (5-10 months) |
| PHC staff training to use ImTeCHO web interface and mobile application along with refresher training | All PHC staff of control and intervention area | 2-3 days | Training phase (5-10 months) |

There is a strong rationale for the requirement of “intervention maturation” phase. Using mobile phone technology requires not only acquiring new skills but organizational change about performing same tasks differently with use of technology. Such change will need to be nurtured and matured before its effectiveness can be evaluated. Based on SEWA Rural’s experience with use of mobile phone technology by frontline workers, each ASHA will have to undergo 3 phases during maturation period: initial training (approximately 3 days), intensive support for first month after training (on the job support) and maintenance support for rest of the intervention (in form of mHealth Facilitator). Considering the scale of intervention area, approximately four months will be required. Also, each ASHA needs to use mobile phone at reasonable times in field setting to get used to the newly acquired skill. Considering small number of pregnant women and newborn in a particular village, few months will be required to get her used to making home visits using mobile phones. Considering small number of training and support staff, training will need to occur in phases instead of all at one time.

The PHC staff will also need to get used to the new system. After initial training (of approximately 2-3 days), extra support will be required for first week to handle information about high risk cases and for downloading and using monthly reports to conduct performance monitoring. Also, support will be required to get PHC staff used to alerts related to supply management and payment of incentives.

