**Figure 5 Organogram**

**Investigator from govt**

Medical officers for Block 1

Medical officers for Block 2

Medical officers for Block 3

ANM for PHC 1

ANM for PHC 2

ANM for PHC 3

All ASHA for that PHC

Medical officers for Block 4

ASHA facilitators for that PHC

The mHealth facilitators will send SMSs to each ANM and medical officer every morning based on complicated cases identified by ASHAs over last 24 hours in addition to scheduled follow up of complicated cases identified over last few days. The ANM will make home visits or contact ASHA for cases with severe complications, confirm diagnosis, assess the status of the patient and try to convince household to refer the case a health facility. In case the family is unable to go to health facility then the ANM will provide treatment on the spot. Such treatment would include providing counseling, giving drugs, including approved antibiotics. The ANM will ensure that the ASHA is informed about the treatment plan and has clear understanding about what she needs to do over next few days, especially to ensure compliance with treatment. Along with attending to complicated cases, ANM will monitor activities of ASHAs.

The mHealth Facilitator will be first contact for ASHAs and other users to report any problem with mobile phone/application and other related issues arising from use of mHealth solutions. The mHF will NOT be involved in patient care or monitoring tasks and will not get in existing working arrangement within the govt. This person will facilitate use of mHealth solutions in existing govt system only.

Some of the specific tasks that mHF will undertake are:

- First contact person in case of any technology/mobile phone/ImTeCHO application related problems encountered by any users (ASHA, PHC staff). In such cases, ImTeCHO facilitator will troubleshoot the problem. If indicated, facilitator will escalate the problem to appropriate authority.
- Manage migration/duplicate cases/append case/death reporting through his/her login on web interface
- Attend PHC meetings for a brief time to troubleshoot any problems with mobile phones, motivation, including distribution of monthly ImTeCHO newsletter and update users about any changes in the application.
- Monitoring of adherence to the ImTeCHO intervention through use of innovative process indicators

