## 16.4 General study implementation

This will be reviewed during once a month meeting at head-quarter to be attended by on-site investigators and mHealth facilitators. Progress of the implementation will be assessed against proposed timeline. These meetings will be a platform to address issues identified during implementation of the project.

Steering committee meeting will be organized every twelve months during which issues related to coordination among various stakeholders will be discussed. Schedule of all monitoring and logistic meeting is indicated Table 12. It should be noted that regular meetings similar to ASHA and ANM review meetings are expected to take place now (in absence of the study) as per the protocol from the Ministry of Health and Family WelfareError: Reference source not found.

**Table 12** Schedule of meetings for quality assurance

| Name of meeting | Goal of meeting | Location | Frequency | Attendees |
| --- | --- | --- | --- | --- |
| PHC meetings (control and intervention area) | Review and support ASHA activities | PHC | Monthly | ASHAs, ANMs, medical officer and PHC staff, mHF |
| Implementation review meeting | Review process indicators and implementation related issues | Chief District Health Officer Office | Quarterly | Investigators, medical officers |
| Data collection review meeting | Review data collection | Head quarter* | Monthly during data collection period | On-site investigators, data collectors |
| Steering committee meeting | Review implementation of intervention | Head quarter | Once every twelve months | Steering committee member, investigators |
| Data Safety and Monitoring Board meeting | Review issues related to data safety and monitor data | Head quarter | Once a year | DSMB member, investigators |

*Head quarter mean SEWA Rural main campus at Jhagadia

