## 17.2 Areas of benefit

Whole study patient population will benefit by this study. Pregnant women, newborns, and children in intervention area will receive all components of interventions which are proven to improve health outcomes. In control area, ASHAs will be re-trained to provide traditional care without use of mHealth solutions. ImTeCHO will provide support to all health workers at PHC level to make their existing job easier, effective and enjoyable. ASHAs stand higher chance of receiving timely and accurate incentives using mHealth solutions. ASHAs will have access to ANM and referral hospital in case a complicated case is identified. PHC staff will be benefitted as calculation of incentives and supply management will be less effort intensive. ANMs will have their monthly reports prepared automatically and on timely basis; thus, saving large number of man-hours.

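### Two operational tables give control PHCs parts of the ImTeCHO intervention (staff training and the facilitator's presence at meetings), contradicting the usual-care comparator

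*Protocol*

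**What the plan says.** **Training table (section 13.1.2, Table 12).** The last row is headed "PHC staff training to use ImTeCHO web interface and mobile application along with refresher training" and its trainees are "All PHC staff of control and intervention area". In the same table, both rows that prepare ASHAs to use ImTeCHO are limited to "All ASHAs of intervention area".

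**Meeting table (section 16.4, also numbered Table 12).** The row "PHC meetings (control and intervention area") gives the attendees as "ASHAs, ANMs, medical officer and PHC staff, mHF", with no restriction by arm. Section 13.1.4 describes what the mHF does there: "Attend PHC meetings for a brief time to troubleshoot any problems with mobile phones, motivation, including distribution of monthly ImTeCHO newsletter", and also updates users on changes in the application.

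**Comparator.** Section 11 states: "The control area will continue to receive usual health services from government and other providers". Section 5.3 (Table 7) likewise defines the comparator as usual practice. Section 17.2 adds: "In control area, ASHAs will be re-trained to provide traditional care without use of mHealth solutions".

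**Status of the two items.** Section 5.3 lists the web interface for PHC staff and the mHF under the intervention. Section 10.2 lists the mHF and two to three days of ImTeCHO training for PHC staff among the intervention's components. Section 6.2 gives the reason for randomising by PHC: PHC staff are the main users of the web interface, and this unit limits contamination.

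**The concern.** Field teams schedule from tables of this kind. Taken literally, they would train control medical officers, ANMs and support staff on ImTeCHO and place the facilitator in control PHCs' monthly meetings. Supervision and support by PHC staff is one of the three ways in which the intervention is meant to work (section 1), and these are the people whose separation between arms justified PHC randomisation.

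Two things are at stake. The comparator could no longer be reported as usual practice. And if control supervision changed as a result, the difference between arms would probably shrink. MACCI has little reserve for that, since the sample size was set for 80% power at the full 15-point difference.

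**Working it through.** **1. Do the passages conflict?**

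| Item | Operational table | Rest of the protocol |
|---|---|---|
| ImTeCHO training of PHC staff | Both areas (13.1.2) | An intervention component (10.2). Section 10.3 describes about 250 ASHAs and the PHC staff being trained to implement the intervention; section 9.1 puts 250 to 300 ASHAs in the intervention area alone, so this describes that arm |
| mHF at PHC meetings | Both areas (16.4) | An intervention component (5.3, 10.2) whose meeting tasks all concern ImTeCHO (13.1.4) |
| Control arm | Receives both items | Usual practice (5.3, 11), without mHealth (17.2) |

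A later sentence in section 10.3 repeats that PHC staff will be trained but names no arm. No statement keeps the mHF out of control meetings. The conflict is therefore real and is not resolved elsewhere in the protocol.

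**2. The plan's own sample size.** Inputs from section 8 and Table 9: MACCI 0.36 against 0.51; two postnatal visits 0.46 against 0.66; two-sided 5%; 80% power; ICC 0.02; 22 ASHAs per PHC (25 less 3).

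- Design effect = 1 + (22 − 1) × 0.02 = 1.42.
- n per arm = [1.96·√(2p̄q̄) + 0.8416·√(p₀q₀ + p₁q₁)]² / (p₁ − p₀)².
- MACCI: n = 171, and 171 × 1.42 / 22 = 11.04 PHCs (10.81 with unpooled variance). Stated: 11.
- Two visits: n = 96, and 96 × 1.42 / 22 = 6.20 PHCs (5.99 unpooled). Stated: 6.

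Both stated figures are reproduced to within rounding.

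**3. Illustrative dilution.** Let f be the share of the effect that reaches the control arm. The protocol gives no value, so f is an assumption. The control rate becomes p₀ + f(p₁ − p₀). With 11 PHCs per arm the effective number of ASHAs is 11 × 22 / 1.42 = 170.4, and

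power = Φ{ [d·√170.4 − 1.96·√(2p̄q̄)] / √(p₀q₀ + p₁q₁) },

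where d is the diluted difference and p₀ the diluted control rate.

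| f (assumed) | MACCI difference | MACCI power | PHCs per arm for 80% (MACCI) | Two-visit difference | Two-visit power |
|---|---|---|---|---|---|
| 0 | 15.0 points | 0.80 | 11.0 | 20 points | 0.96 |
| 10% | 13.5 | 0.71 | 13.7 | 18 | 0.92 |
| 20% | 12.0 | 0.61 | 17.4 | 16 | 0.85 |
| 30% | 10.5 | 0.49 | 22.8 | 14 | 0.75 |

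The powers assume that all 11 PHCs per arm are retained. Section 8 counts 23 eligible PHCs for both arms together, so lost power could hardly be bought back with more clusters.

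**The case against.** The strongest reply is that these are drafting slips and that little would follow from them.

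- **The training row merges two trainings.** Section 13.1.2 distinguishes refresher from ImTeCHO training. A refresher for both arms and ImTeCHO training for one, forced into a single row, would produce this trainee cell. Section 10.3 supports that reading.
- **The meeting row may pool attendees.** Section 16.4 notes that such review meetings are expected without the study. The mHF's meeting tasks presuppose ImTeCHO users, and no other section gives the mHF a task in a control PHC.
- **The route to contamination is limited.** The web interface shows data entered on phones by ASHAs and ANMs. The training table keeps application training and access to the production server for intervention ASHAs, and section 11 says that the existing government SIM scheme provides no handsets. Control staff would have little ImTeCHO data to act on, and the primary outcomes depend largely on what ASHAs do.

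Most of this stands as a limit on the size of the effect. It does not remove the contradiction: a slip in an operational table can still be carried out, and contact with the facilitator or adoption of ImTeCHO-style supervision needs no control-area data.

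A reader might infer that control PHC staff are expressly restricted to a refresher. The documents do not say so: sections 11 and 17.2 describe training of control ASHAs and are silent on control PHC staff. A reader might also infer that the randomisation unit or the comparator was badly chosen. Both are stated consistently, and only the two table rows depart from them.

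**Conclusion.** The point holds as an internal contradiction that should be corrected. Two tables assign intervention components to control PHCs, against the comparator in sections 5.3, 11 and 17.2, the reason for cluster randomisation in section 6.2, and the direction of section 10.3. Following them could expose control supervisors to the intervention and could bias the comparisons towards no difference.

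It would be tempting to conclude that both primary comparisons are biased, or that MACCI power is really about 61%. Neither is supported. Exposure of control PHC staff is a risk rather than a demonstrated effect, and the leak fractions rest on nothing in the protocol. The power figures show only how sensitive each outcome would be. MACCI starts with no margin and drops below 80% at an assumed 10% leak, while the two-visit outcome still has about 85% at 20% and falls below 80% only by 30%. The case for correction rests on the contradiction, whatever the true leak.

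**What to change.** - **Section 13.1.2, training table:** split the last row. Give ImTeCHO web and mobile training to PHC staff of the intervention area only. If control PHC staff are meant to have a refresher, list it in its own row, stated to carry no ImTeCHO content.
- **Section 16.4, meeting table:** keep routine PHC meetings for both areas, but show the mHF as attending in intervention PHCs only.

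Both changes bring the tables into line with sections 5.3, 10.3, 11 and 17.2. The cost is an edit to two table rows. No data collection is added, and ImTeCHO training sessions and facilitator attendance in control PHCs are saved. The change should be made before the training phase (months 5 to 10), because it fixes what the control arm receives.

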### 13.1.4 Implementation of ImTeCHO intervention and field organization

As this study does not assign any new tasks to ASHAs beyond envisioned by the government, she will continue performing her duties as before except now she will use mobile phone. ASHAs will be making home visits and will use mobile phones as job aid. Detailed description of how ASHAs will use mobile phones can be found in section 10.1.1. ASHAs will assist ANMs during monthly VHND and enter information about blood pressure, haemoglobin, per abdominal examination, weight and urine examination as recorded by the ANM. ASHAs will come to PHC for monthly review meetings. She will report any technical problem to mHealth facilitator.

**Figure 5 Organogram**

**Investigator from govt**

Medical officers for Block 1

Medical officers for Block 2

Medical officers for Block 3

ANM for PHC 1

ANM for PHC 2

ANM for PHC 3

All ASHA for that PHC

Medical officers for Block 4

ASHA facilitators for that PHC

The mHealth facilitators will send SMSs to each ANM and medical officer every morning based on complicated cases identified by ASHAs over last 24 hours in addition to scheduled follow up of complicated cases identified over last few days. The ANM will make home visits or contact ASHA for cases with severe complications, confirm diagnosis, assess the status of the patient and try to convince household to refer the case a health facility. In case the family is unable to go to health facility then the ANM will provide treatment on the spot. Such treatment would include providing counseling, giving drugs, including approved antibiotics. The ANM will ensure that the ASHA is informed about the treatment plan and has clear understanding about what she needs to do over next few days, especially to ensure compliance with treatment. Along with attending to complicated cases, ANM will monitor activities of ASHAs.

The mHealth Facilitator will be first contact for ASHAs and other users to report any problem with mobile phone/application and other related issues arising from use of mHealth solutions. The mHF will NOT be involved in patient care or monitoring tasks and will not get in existing working arrangement within the govt. This person will facilitate use of mHealth solutions in existing govt system only.

Some of the specific tasks that mHF will undertake are:

- First contact person in case of any technology/mobile phone/ImTeCHO application related problems encountered by any users (ASHA, PHC staff). In such cases, ImTeCHO facilitator will troubleshoot the problem. If indicated, facilitator will escalate the problem to appropriate authority.
- Manage migration/duplicate cases/append case/death reporting through his/her login on web interface
- Attend PHC meetings for a brief time to troubleshoot any problems with mobile phones, motivation, including distribution of monthly ImTeCHO newsletter and update users about any changes in the application.
- Monitoring of adherence to the ImTeCHO intervention through use of innovative process indicators
- Remote supervision of ASHAs through phone in form of once a month performance review phone call by using information from ImTeCHO wed interface. Additionally, daily tracking of pre defined performance parameters available through web interface and follow up actions, if required. This includes contacting ASHAs for long overdue tasks, pending entry for mamta divas services and pending login for long stretch of time.
- Occasional field visit (support visit) to those ASHAs whose performance parameters within ImTeCHO is consistently poor and to provide ongoing training/supervision/motivation.
- SMS ANMs to inform about high risk cases
- Attend two-monthly ImTeCHO facilitators’ review meeting with program coordinator. There will be one program coordinator for ten facilitators.
- Facilitate calculation and disbursement of ImTeCHO related incentives
- Will NOT get involved in patient care, supply replenishment, grievance redressal etc.
- Overall, facilitator will spend 80% of time in office and 20% in field.

Medical officers will be responsible for tracking of high risk cases on daily basis in addition to presiding over routine monthly ASHAs meeting . The medical officer will assess performance of ANMs and ASHAs during these meetings in addition to supporting them in form of addressing any supply issues and payment of incentives. Complicated cases will be discussed during these meetings.

PHC support staff will use web interface to manage incentives and supplies. The staff will review and edit monthly ASHA activity report which will be used by ImTeCHO to automatically calculate incentives. The staff will enter information in web interface about payments made to ASHAs. Similarly, information about status of supplied and any “stocked out” items will be available on web.

SEWA Rural’s administrative staff and mHealth facilitators will manage migration, users, duplicate cases, amendment of any existing cases along with transcribe any information relayed through audio by ASHAs.

